# A pilot cluster randomised controlled trial to investigate the addition of direct access to physiotherapy to usual GP-led primary care for adults with musculoskeletal pain: the STEMS pilot trial protocol (ISRCTN23378642)

**DOI:** 10.1186/s40814-015-0020-4

**Published:** 2015-07-17

**Keywords:** Physiotherapy, Direct access, Self-referral, Musculoskeletal, Cluster trial, Pilot

## Abstract

**Background:**

Musculoskeletal problems are common, accounting for up to 30 % of general practitioner (GP) consultations and are a major cause of chronic disability worldwide. Demand for health care for musculoskeletal conditions is likely to continue to rise given the ageing population and the increasing impact of these common painful conditions. Physiotherapists are well equipped to deliver evidence-based management for these conditions. Direct access allows patients to access physiotherapy without seeing their GP or another referring practitioner first; however, for most patients in the UK, access to National Health Service physiotherapy is controlled through GP referral.

**Methods/Design:**

The aim of this pilot, pragmatic, cluster trial is to assess the feasibility of a future large trial to compare the clinical and cost-effectiveness of the additional offer of direct access to physiotherapy versus continuing with usual GP-led primary care alone for adults with common musculoskeletal problems. The pilot will focus on process outcomes to assess feasibility, although performance of the likely outcomes of a main trial will also be assessed. This is a two-arm parallel, cluster RCT where GP practices are the units of randomisation (the clusters), yet data are collected from individual patients with musculoskeletal problems (the participants). A direct access service will be set up in the participating physiotherapy service to provide the option of direct access to patients of the intervention arm practices. Inclusion criteria are broad to reflect the ‘real-world’ operation of an NHS physiotherapy direct access service for patients with musculoskeletal pain. Data collection will be through patient self-reported questionnaires at baseline, 2, 6 and 12 months and medical record review.

**Discussion:**

No previous trials have been conducted into direct access to physiotherapy for patients with musculoskeletal problems. The strengths of the STEMS pilot trial are its size, the length of follow-up, and collection of process, clinical and cost outcomes to fully inform a future main trial to meet calls to provide robust trial evidence of the impact on clinical outcomes, work loss and costs to provide clinicians and service funders with the high quality trial data they need to guide decisions on the best models of care.

**Trial registration:**

The STEMS pilot trial is registered at Current Controlled Trials: ISRCTN23378642

**Electronic supplementary material:**

The online version of this article (doi:10.1186/s40814-015-0020-4) contains supplementary material, which is available to authorized users.

## Background

Musculoskeletal problems are common and costly and increase with age. Musculoskeletal conditions account for up to 30 % of general practitioner (GP) consultations [1], and yet it is estimated that only between 30–40 % of individuals with musculoskeletal problems consult their GP [2–4]. The Global Burden of Disease Study shows that musculoskeletal conditions are a major cause of chronic disability worldwide and have increased markedly in the last decade [5]. Given the ageing population and the increasing impact of these common painful conditions, the demand for musculoskeletal healthcare is set to rise and health care delivery systems will need to develop a ‘coherent policy for dealing with musculoskeletal disorders’ [5]. Best evidence for many of these musculoskeletal conditions recommends treatments such as advice, education, exercise, manual therapy and acupuncture [1, 6, 7]. Such treatments are cost-effective [8] and are those that professionals such as physiotherapists are equipped to deliver. Early physiotherapy intervention for musculoskeletal problems reduces sick leave and helps prevent acute problems becoming chronic [1, 9–12]. However, for most patients in the UK, access to National Health Service (NHS) physiotherapy is controlled through GP referral.

Direct access to physiotherapy is a system of access in which ‘patients are able to refer themselves to a physiotherapist directly without having to see anyone else first or without being told to refer themselves by a health professional’ [13]. Although direct access is well established in private practice in the UK and in other countries including Australia, the Netherlands, some states within the USA and in Scotland [14–17], uptake in the NHS in England has been very limited. Funders of physiotherapy services express concerns about creating excessive demand and associated costs and where direct access services have been established at least one in England has been stopped due to funding being withdrawn [18].

To date, evidence about direct access to physiotherapy comes from observational studies only. These have suggested that direct access may reduce GP workload [19] with estimates of a 20 % reduction in multiple GP consultations [20]. An evaluation in the Netherlands reported that in the first 12 months of direct access, patients referring themselves accounted for 22–28 % of all physiotherapy referrals [14, 21]. Reported patient benefits of direct access are greater freedom of choice and improved access to musculoskeletal care [13, 14, 19, 22], since direct access allows the patient to opt for physiotherapy when they are in most need. There are also some suggested cost-benefits, with GP referral costing £133 an episode and an episode of care through direct access costing £100 [23].

A global review of direct access to physiotherapy has identified professional legislation, the medical profession, politicians and policy makers as both barriers to and facilitators of direct access [24]. A European-focused review of direct access services concluded that clinicians, managers and service funders need high quality trial data on both clinical and cost-effectiveness to guide decisions on the best models of care [25]. In addition, an independent evaluation of the observational UK Department of Health pilots of direct access to physiotherapy [13] concluded that robust evidence of the impact on clinical outcomes, work loss and costs are lacking due to important flaws in observational study designs and that a randomized controlled trial (RCT) comparing areas that do and do not offer direct access is required to provide robust evidence about direct access [26].

The most appropriate design for a RCT to evaluate direct access is a non-inferiority cluster RCT that compares the clinical and cost-effectiveness of the additional offer of direct access to physiotherapy versus continuing with usual GP-led care alone for patients with musculoskeletal conditions in primary care. However, given that this involves developing a new direct access service, it is important to conduct feasibility and pilot work first in order to fully inform a future main trial.

### Overall aim

The overall aim of the STEMS pilot trial is to assess the feasibility of a future large trial to compare the clinical and cost-effectiveness of the additional offer of direct access to physiotherapy versus continuing with usual GP-led primary care alone for adults with common musculoskeletal problems.

### Objectives

The objectives of the STEMS pilot trial include both process and research objectives. Analysis of the process objectives will enable the feasibility of a larger cluster RCT to be assessed. They focus on the feasibility of working with general practices and physiotherapy services to develop and set up a direct access to physiotherapy service, the acceptability of direct access and the ability to both recruit and retain participants in the research evaluation.

#### Process objectives

To assess the number of practices approached and agreeing to take part (baseline) and the engagement of GP practices and physiotherapy services to stay in the pilot trial through follow-up (12 months)To develop and test approaches to market a new direct access service in ways that ensure a sufficient proportion (at least 20 %) of patients access physiotherapy through self-referral to make a main trial feasible (assessed through referral methods as physiotherapy service)To assess the feasibility of establishing a physiotherapy direct access service that can respond to demand and avoid increases in waiting times or staffing levels (monitored throughout the recruitment period)To estimate participant recruitment rates in both control and intervention practices (assessed at end of recruitment)To explore any evidence of selection bias in participants recruited to the research evaluation from the control and intervention practices (assessed through participant characteristics at baseline)To estimate retention of participants in the research evaluation at each follow-up time-point across both control and intervention practices

#### Research objectives

The pilot trial will also provide a useful test of outcome data collection methods, including key clinical outcomes, and provide information on the likely changes in these outcomes in the control and intervention groups. Whilst a main trial will provide the definitive test of the difference between trial groups on these clinical outcomes, the pilot has the following research objectives:To investigate likely changes in the primary clinical outcome measure (physical health measured using the SF36v2 Physical Component Summary)To investigate likely changes in secondary outcome measures (overall perceived change, mental health, pain self-efficacy, quality of life, understanding of the condition, experience of care and convenience and accessibility of service)To provide an early estimate of the costs, both healthcare and societal costs, in both intervention and control groupsTo explore the use of willingness to pay (WTP) methodology to capture the strength of patient preferences for direct access to NHS physiotherapyTo confirm the parameters needed for a realistic sample size calculation for a future main cluster RCT

## Methods

### Design

The design is a pilot, pragmatic, cluster RCT in general practice and physiotherapy services. The most appropriate trial design is a simple, two-arm parallel, cluster RCT where GP practices are the units of randomisation (the clusters), yet data are collected from individual patients with musculoskeletal problems (the participants). This design overcomes the problem of contamination between arms and the problems associated with individually consenting and randomising patients to a trial testing service-level changes. A main trial would employ a non-inferiority design as it will be essential that the intervention is as least as good as usual GP-led care in terms of patients’ clinical outcomes (physical health measured using the SF36v2 Physical Component Summary).

A repeated measures design will be adopted, whereby participants will complete the questionnaires at baseline, 2, 6 and 12 months. Each participant’s involvement in the trial is for 12 months, during which time they will all have access to usual GP-led primary care. No analysis of clinical outcomes will be undertaken until the 12-month follow-up time-point.

### Setting and clusters

The setting is primary care in England for adults with musculoskeletal problems (GP practices and linked NHS physiotherapy services). GP practices are the unit of randomisation, and thus, patients follow the care pathways to which the practice is randomised. In this pilot, RCT practices will be stratified only on practice size, but in a main trial, practices would also ideally be stratified by index of deprivation. Randomisation of GP practices will be undertaken by an independent statistician. GP practices will be randomised to one of two arms, either to continue with usual GP-led primary care for musculoskeletal patients with the addition of the offer of a self-referral physiotherapy pathway (intervention group) or to continue with usual GP-led primary care alone (usual care control group). Practices will be randomised according to a computer-generated random numbers stratified by the practice size (small or large) in the ratio 1:1. In a main study, we would plan to further stratify by practice setting and area level deprivation (through minimisation) in order to ensure balance in key practice characteristics in each arm of the trial.

GP practices are eligible to take part if they meet the following criteria: they are within the Vale Royal Clinical Commissioning Group area of Cheshire and the Clinical Research Network (CRN); they are a group practice, currently referring musculoskeletal patients to NHS physiotherapy services; they do not currently offer direct access to physiotherapy; and they are willing to test direct access. The balance between scientific considerations and the need for consent is a known issue for cluster trials [27]. Informed consent for practices to participate will be provided by the senior GP partner in each practice acting as ‘guardian’ for patients in their care. Patients will follow the care to which their practice is randomised with identical patient information for both arms providing general information about the study, explaining that their local musculoskeletal services are being evaluated using patient self-reported clinical outcomes and medical record review. Individual patients will therefore be able to opt out of data collection.

### Participants

The inclusion criteria have been designed to be as broad as possible to reflect the ‘real-world’ operation of an NHS physiotherapy direct access service for patients with musculoskeletal pain.

Inclusion criteria are all adults consulting participating GP practices or physiotherapy services with musculoskeletal problems (for either their first consultation for a new episode of musculoskeletal pain or a reconsultation).

Exclusion criteria are: under 18 years old at the time of consultation; consulting with non-musculoskeletal problems; unable to provide their own consent to the research evaluation; undergoing palliative care; severe learning disabilities; housebound or in nursing home accommodation; and unable to communicate in English (although all potential participants will be offered the opportunity to telephone a research nurse, blinded to practice allocation, for help in completing the paperwork).

### Participant identification and recruitment

Following randomisation of GP practices, potentially eligible participants will be identified through one of three methods.

Method 1: Patients consulting GP practices with a musculoskeletal problem will have a musculoskeletal Read code^1^ (entered by GPs or nurse practitioners) entered into their computerised medical record. A member of the GP practice team, or CRN staff, will download the details of patients with these Read codes twice weekly checking for exclusion criteria and then forward these details to a CRN administrator. GPs will be able to exclude any patients they perceive as being particularly vulnerable and unsuitable to approach for involvement in research by using a dedicated exclusion code set up for the study.

Method 2: In addition, for those GP practices randomised to also offer direct access to physiotherapy, patients who self-refer to physiotherapy will be identified when they forward a completed self-referral form to the physiotherapy service or telephone the physiotherapy administrator for help in completing a form. As in method 1 the details of identified patients will be forwarded to a CRN administrator.

Method 3: Patients referred by GPs or practice nurses to the physiotherapy service, but not identified in method 1 due to an absence of an appropriate Read code in the computerised medical records, will be identified from the physiotherapy administration database. A physiotherapy administrator will download the details of all patients referred from the participating GP practices twice weekly and forward these details to a CRN administrator. Duplication checks will ensure that eligible patients are not invited to take part in the research more than once.

All eligible patients will be mailed a STEMS study pack (letter of invitation, participant information leaflet (see Additional file 1), consent form, baseline questionnaire and pre-paid return envelope). Participants will not be individually consented to randomisation, rather participants in both arms of the trial will be asked to give written consent to take part in a study investigating musculoskeletal problems and local health services, consisting of the baseline and follow-up questionnaires (at 2, 6 and 12 months) and to allow the research team access to their medical records to review healthcare use for their musculoskeletal problem. Patients interested in participating will be offered the option of telephoning a research nurse, blinded to practice allocation, who will answer any questions and support those who need it to complete the consent form and questionnaire over the phone. Participants who consent to participation will return the completed questionnaire and consent form to the research centre, and the research team will then have access to their personal identification details. Participants completing the consent form but having missing data at baseline on the primary outcome measure (the SF36v2), such that a Physical Component Summary score cannot be calculated, will be contacted by telephone to collect the missing data. At each data collection time-point (baseline, 2, 6 and 12 months), non-responders will be mailed a postcard reminder 2 weeks after mailing of the trial study pack and a repeat study pack 2 weeks after the reminder postcard. At 6- and 12-month follow-up, non-responders will subsequently be mailed a very brief minimum data questionnaire, consisting of the SF-36v2 and the single Global Assessment of Change question only. Telephone collection of minimum data will be attempted for the remaining non-responders.

This method of recruitment has been used successfully in previous studies. Our processes ensure that all eligible patients will be identified, recruited through postal study packs (with telephone support where needed) with identical information about the evaluation study given to those in both arms of the trial [27]. Participants’ GPs will be notified of their consent to participate in the research evaluation. Participating general practices will be supported to assist with identification of potentially eligible participants for the STEMS pilot trial through small practice payments to reimburse their time for screening patient lists. The physiotherapy service will be supported to participate through financial reimbursement for the time taken from service delivery for participation in the training programme. Participants will not receive any payments or other incentives to take part in the STEMS pilot trial or to return baseline or follow-up questionnaires. A flowchart illustrating the STEMS pilot trial is shown in Fig. 1.

**Fig. 1 Fig1:**
[figure not shown]
Flow chart of the STEMS pilot cluster randomised trial

### Methods for protecting against sources of bias

Allocation concealment for participating GPs and physiotherapists is not possible, and therefore, to prevent recruitment bias, neither of these groups of clinicians will be involved in recruiting participants into the research evaluation. Instead eligible participants will be identified from electronic GP medical records and from the physiotherapy service database, conducted by CRN staff. We will follow the CONSORT guidelines for both cluster trials and non-inferiority trials [28, 29]. In an ideal world, the comparison would be all patients who have a musculoskeletal problem in the participating practices during the study period, whether or not they attend their GP and/or physiotherapy service, but clearly this is not possible. Therefore, all patients who consult their GP practice (control arm) will be compared with all patients who consult their GP or physiotherapy service (intervention arm) with a musculoskeletal condition. Patients who directly access physiotherapy may be different in important ways to those who consult their GP, which is a limitation of the design. Therefore, in the pilot trial, we will investigate whether the number of consulters (to GPs only in the control arm and to either GPs or physiotherapists in the intervention arm) that have been identified in each arm are similar, whether there appears to be any differential uptake to the research evaluation in the two arms and whether the baseline characteristics of participants in each arm are similar.

Both primary and secondary outcomes are based on self-report postal questionnaires; therefore, no investigator bias will be introduced at assessment. The research nurses involved in helping patients to complete questionnaires and minimum data collection will be based in the Clinical Research Network, not in participating practices, and will be kept blind to practice allocation. Success of blinding will be recorded on the Minimum Data Collection form. In addition, the trial statistician undertaking the analysis will also be blind to practice allocation. Using validated outcome measures for self-report will guard against measurement error. Quality control including data entry, coding, security, storage and management will be performed according to the Standard Operating Procedures of the Keele Clinical Trials Unit. A random 10 % of the participants’ data entered will be compared with the paper versions to check data entry accuracy. Data accuracy will be audited and accuracy rates recorded. Loss to follow-up will be minimised by implementing standardised reminder procedures and minimal data collection for non-responders. Participants will be free to withdraw from the research at any time without having to give any explanation. Where possible, we will collect information about the reasons for withdrawal. All records will be kept confidential and data sets for each participant will be identified by the patient’s participant number. Analysis will be performed on an intention-to-treat (ITT) basis using the full set of available data (mixed model and multiple imputation of missing data). Patients self-referring or being GP-referred receive equitable treatment, for example, in the length of wait to first physiotherapy contact once they are logged on the physiotherapy administration system. The physiotherapists participating in the trial will provide physiotherapy care to patients from both arms of the trial (initiated from traditional GP referral in the control arm versus from both traditional GP referral and patient self-referral in the intervention arm). As this trial is investigating the addition of direct access to physiotherapy, the physiotherapy care provided will be determined by clinical need and assessment findings and will therefore be consistent with routine practice and not differ for patients in different arms of the trial.

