#### Evidence of selection bias

Since this is a pilot trial with only four clusters randomised, it is likely that there will be some imbalance between participants in each of the treatment arms on one or more baseline characteristics. Baseline comparisons will be carried out to detect any substantial differences between participants recruited from the control and intervention arms. This will be done by scrutinising the baseline table for any serious imbalances in observable baseline variables and the trends of the imbalance if any. The recruitment rates will also be estimated and compared between the control and intervention arms. We will examine the size of any imbalances and decide if there is evidence of systematic selection bias in the types of patients being recruited in control versus intervention arms. Any systematic imbalance in the sense that one arm is consistently favoured by the imbalances may not reflect chance alone and may suggest selection bias.

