#### Explore generalisability of the sample

Anonymised data on key baseline characteristics (age, gender and index of multiple deprivation (from post-codes)) of those who are invited but who do not participate will be compared with those who do participate. Key baseline characteristics will be compared between those participants followed up and those lost to follow-up at each time-point. Key characteristics of the participants recruited using each recruitment method will be reported. Delays in return of questionnaires (>35 days from initial mailing date) will also be compared between the two arms.

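### The stated safeguard against recruitment bias does not match the identification procedure, which lets unblinded GPs exclude patients after randomisation, and the planned checks do not isolate those exclusions

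*Protocol article*

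**What the plan says.** Under Methods for protecting against sources of bias, the protocol article accepts that "Allocation concealment for participating GPs and physiotherapists is not possible". It gives this as the reason why "neither of these groups of clinicians will be involved in recruiting participants into the research evaluation", and adds that identification from GP records and the physiotherapy database is done by CRN staff.

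Participant identification and recruitment sets out the procedure: "Following randomisation of GP practices, potentially eligible participants will be identified through one of three methods". In Method 1 the trigger is a musculoskeletal Read code that a GP or nurse practitioner enters. Then "A member of the GP practice team, or CRN staff, will download the details of patients with these Read codes twice weekly"; the same people apply the exclusion criteria. In addition, "GPs will be able to exclude any patients they perceive as being particularly vulnerable and unsuitable to approach for involvement in research", by means of an exclusion code created for the study. The same section reimburses practices for screening lists and claims that the processes find every eligible patient.

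The checks are spread over several sections:
- numbers of consulters identified per arm, uptake per arm and baseline similarity (Methods for protecting against sources of bias);
- numbers identified and recruited by each method, and recruitment as a share of those invited (Feasibility of study recruitment and retention);
- GP consultation rates before and during the study (Table 1);
- age, gender and deprivation "of those who are invited but who do not participate will be compared with those who do participate" (Explore generalisability of the sample).

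On interpretation, Evidence of selection bias says: "Any systematic imbalance in the sense that one arm is consistently favoured by the imbalances may not reflect chance alone and may suggest selection bias".

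**The concern.** A cluster trial that finds its participants after allocation is exposed to recruitment bias wherever someone who knows the allocation influences who is approached. The protocol recognises this and claims to have closed the route, but its own procedure leaves part of it open. A GP's judgement that a patient is unsuitable to approach is made with the allocation known, and a reader who relies on the bias section would not learn that it happens.

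Exploring selection bias is one of the pilot's six process objectives. If GP exclusions are not counted separately, the pilot cannot say how large this filter was or whether it differed between arms. If one-sided baseline imbalance is then read as a pointer to selection, ordinary differences between practices may be mistaken for it. Either error would misinform the design of the main trial.

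**Working it through.** **1. The two descriptions compared.**

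| Step | Bias section | Recruitment section |
|---|---|---|
| Trigger for identification | Electronic records | Read code entered by a GP or nurse practitioner |
| Download and screening, Method 1 | CRN staff | Practice team member or CRN staff |
| Download, Method 3 | CRN staff | Physiotherapy administrator |
| Removal before invitation | Not mentioned | GP judgement, through the study code |
| Timing | Clinicians know the allocation | After practices are randomised |

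Mailing and consent do run without clinicians, so the conflict concerns identification and exclusion.

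**2. What the uptake check can register.** The protocol's own planning figures reproduce: 100 consulters a month × 0.80 eligible × 0.50 responding × 4 practices × 6 months = 960 at baseline, and 960 × 0.80 = 768 followed up. Eligible patients per arm are 80 × 6 × 2 = 960.

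Assume that GPs exclude 10% in one arm and 2% in the other, and that the remainder respond at the planned 50%:
- arm A: invited 960 × 0.90 = 864, recruited 432, uptake 432/864 = 50%;
- arm B: invited 960 × 0.98 = 941, recruited 470, uptake 470/941 = 50%.

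Uptake is the same although 96 patients were removed in one arm and 19 in the other. The counts of patients identified might differ, but the text does not say whether they are taken before or after GP exclusion. Direct access may itself change how many patients consult.

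**3. How often imbalances line up by chance.** Let k baseline variables have arm differences that are normal with mean zero (no selection) and equal correlation ρ. Then

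P(all favour one arm) = 2 ∫ Φ(z√(ρ/(1−ρ)))^k φ(z) dz,

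which is 2/2^k at ρ = 0 and 2/(k+1) at ρ = 0.5. The documents give neither the k to be judged nor ρ; both are assumed. Analyses of clinical outcomes lists 18 baseline items, so k = 18 is shown beside k = 8.

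| ρ | k = 8 | k = 18 |
|---|---|---|
| 0 | 0.8% | below 0.01% |
| 0.3 | 10% | 2.6% |
| 0.5 | 2/9 = 22% | 2/19 = 10.5% |
| 0.7 | 39% | 26% |

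One-sided imbalance would be strong evidence only if the variables were close to independent. Several of those listed (physical and mental component scores, physical function, self-efficacy, pain duration, risk of persistent problems, comorbidities) are plausibly correlated. Demographic items are likely to be less so.

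**4. What two practices per arm can resolve.** With 960/4 = 240 participants per practice and a total SD of 1, the standard error of an arm difference is √(ICC + (1 − ICC)/240), and t(0.975) on 2 degrees of freedom is 4.303. The ICC is an assumption.

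| ICC | Standard error (SD) | 95% CI half-width (SD) | Chance of a difference above 0.1 SD with no selection |
|---|---|---|---|
| 0.001 | 0.072 | 0.31 | 16% |
| 0.01 | 0.119 | 0.51 | 40% |
| 0.02 | 0.155 | 0.67 | 52% |
| 0.05 | 0.232 | 1.00 | 67% |

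If GPs in one arm removed a fraction f of patients whose mean is 1 SD worse (assumed), the arm mean would move by f/(1 − f): 0.05/0.95 = 0.05 SD or 0.10/0.90 = 0.11 SD. Both lie well inside every half-width in the table.

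**The case against.** The best defence is that recruiting means inviting and consenting. That is done by mailed packs, identical in both arms, with help from research nurses blind to allocation. The exclusion code is openly described and meant for vulnerable patients. This narrows the conflict without removing it, because the bias section extends its safeguard to identification by CRN staff.

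A reader might infer that GP exclusion would be invisible. The documents do not support that: consulters identified per arm, numbers by method, and consultation rates before and during the study could together reveal a large loss. Method 3 also recovers physiotherapy referrals that lack a suitable Read code.

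A reader might also infer that self-referrers in the intervention arm bypass the exclusion code. The text does not say whether their records are checked for it. The wider point, that the arms draw patients from different sources, is already declared a limitation.

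The remark on consistent imbalance is a hedged judgement with no threshold, and it follows an admission that imbalance is likely with four clusters. It should not be described as a decision rule. Nor do the documents say that this check decides progression; their numerical criteria concern recruitment, retention and the direct-access share of caseload.

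Finally, splitting tables by arm is detail that an article may leave to the analysis plan. That is fair for the tabulation alone, but not for a safeguard that the article misstates or an interpretation that it prints.

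**Conclusion.** The point stands in limited form. The protection claimed in the bias section is not the one described in the recruitment section: after randomisation, clinicians and practice staff who may know the allocation influence who is identified, and GPs can remove patients by judgement. The planned checks might show a large loss but do not isolate GP exclusions, since uptake is measured among those invited and the comparison of participants with non-participants has no stated split by arm.

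Reading one-sided imbalance as a sign of selection is weak. Without any selection, complete agreement in direction arises in about 10% to 22% of draws with 8 variables and 3% to 11% with 18, at assumed correlations of 0.3 to 0.5. These figures are illustrations; they depend on the assumed number of variables and on equal correlation. The actual rate of GP exclusion is unknown, and nothing shows that bias will occur. The limits on resolution come from having four practices and would remain under any reporting scheme. This should be corrected, but it does not undermine an exploratory pilot.

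**What to change.** 1. Reconcile Methods for protecting against sources of bias with Participant identification and recruitment, including the statements on practice payments for screening and on finding every eligible patient. Say who codes, screens and excludes, and that GP exclusion takes place with allocation known.
2. Count the study exclusion codes by practice and arm, and start the participant flow before that exclusion.
3. Split the comparison of participants with invited non-participants by arm and report it descriptively.
4. In Evidence of selection bias, state that the direction of imbalance with four practices can neither confirm nor rule out selection bias.

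The code already exists and the comparison is already planned, so the cost is slightly more work for the staff running the searches, together with a weaker stated claim of protection. These steps make the filter visible. They do not allow a difference to be attributed to allocation, because there are still only two practices per arm.
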